### Statistical methods

Endpoints will be evaluated by both intention-to-treat- and per-protocol-analyses. Statistical tests and presentation will be appropriate to the scaling and distribution of the respective variables. Because TRIOMS is planned as a pilot study, there is a statistical analysis of endpoints, but *P*-values will be considered exploratively without confirming generalization of hypotheses about the study treatments. Due to the restricted sample size of the pilot study, sufficiently powerful statistical analysis is not possible. The primary end point will be analyzed using Fisher’s exact test. Secondary endpoints will be analyzed non-parametrically using Mann–Whitney-U-test, due to the small sample size and possible deviations from normality. Frequencies will be compared with the Fisher’s exact test.Because of the exploratory character of the analysis, alpha-adjusting will not be performed. The test level for statistical significance of differences between both treatment arms is defined as *P* = 0.05 (two-sided) for all tests. For statistical analyses use of the following software is planned: SAS, version 9.4 (SAS Institute Inc. Cary, North Carolina, US); SPSS, version 20 (IBM, Armonk, New York, US) and StatXact 6 from CYTEL (Cytel Inc., Cambridge, Massachusetts, US).

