### Outcome parameters

The primary endpoint is the cumulative number of new hyperintense lesions identified on T2-weighted brain MRI during the treatment period of 12 months. Additional secondary MRI endpoints comprise the volume of T2 hyperintense lesions and number and volume of contrast-enhancing T1 hypointense lesions, the proportion of patients without any new T1 hypointense and T2 hyperintense lesions, brain atrophy as determined by brain parenchymal fraction and normalized brain volume 18 [19], and changes in brain metabolism (NAA/Cr-quotient) as determined by MR spectroscopy [20,21]. All MRI investigations will be performed using a 3 Tesla MRI scanner (Siemens Healthcare, Erlangen, Germany. Other secondary clinical endpoints include the annualized relapse rate and the proportion of relapse-free patients. A relapse is defined as *de novo* development, aggravation or re-occurrence of a pre-existing neurological abnormality compatible with MS, which lasts a minimum of 24 hours, is separated by at least 30 days from a preceding clinical event and does not occur in the context of fever or infection. Further secondary endpoints are the disease progression as determined by EDSS (evaluated by an independent neurologist) [17], Multiple Sclerosis Functional Composite (MSFC) [22], depression as determined by the Beck Depression Inventory (BDI) [23] and fatigue as determined by the Fatigue Severity Scale (FSS) [24]. Assessment of all clinical and MRI endpoints will be performed by experienced evaluators blinded to both the clinical data and treatment allocation. Peripheral venous blood (serum, heparinized blood for flow cytometry and PBMC isolation) will be sampled prior to and during the intervention to assess the effect on cellular and soluble components of the immune system. In detail, we plan to monitor the Th1/Th2/Th17 balance by concanavalin A stimulation of fresh heparinized blood and determination of cytokines using the cytokine bead array. In fresh heparinized blood, we will measure the frequency of B cells, CD4+ and CD8+ T cell subpopulations, innate immune cells and quantify the activation and homing markers on these cells by multicolor flow cytometry. We will also assess the number of IL-10-producing B cells by stimulation of fresh isolated PBMCs with 0.1 mg/ml CpG ODN2006 for 72 hr and will add phorbol myristate acetate and ionomycin (PMA+iono) for the last 6 hr and brefeldin A for the last 4 hr in order to block cytokine excretion. Detection of IL-10 producing cells is planned as intracellular staining of IL-10 on CD 19 expressing cells by multicolor flow cytometry. Alternatively, IL-10 we will be measured in the culture supernatants by ELISA with aliquots of supernatant taken from cell cultures before the addition of brefeldin A and PMA+iono to the cultures.

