
### Sample size

Because the present data on the effect of TSO on the development of new T2 hyperintense lesions on brain MRI, which is the primary endpoint of the TRIOMS study, are insufficient for an exact statistical sample size calculation, we have designed the investigation as a pilot study with an *a priori* determined sample size of 25 patients per intervention arm, giving a total of 50 patients. The results of this exploratory analysis could serve as the basis for a further prospective randomized study with a statistically justified sample size.

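### The primary endpoint is a lesion count, but the named test is Fisher's exact test with no categories defined; a rank or count method fits the endpoint and has more power

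*Protocol article*

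**What the plan says.** Under Outcome parameters the protocol article states: "The primary endpoint is the cumulative number of new hyperintense lesions identified on T2-weighted brain MRI during the treatment period of 12 months". That is one count per patient. The same section lists, as a separate secondary endpoint, "the proportion of patients without any new T1 hypointense and T2 hyperintense lesions".

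Under Statistical methods four sentences bear on the choice of test:
- the general rule: "Statistical tests and presentation will be appropriate to the scaling and distribution of the respective variables"
- the primary analysis: "The primary end point will be analyzed using Fisher’s exact test"
- the secondary analyses: "Secondary endpoints will be analyzed non-parametrically using Mann–Whitney-U-test, due to the small sample size and possible deviations from normality"
- categorical outcomes: "Frequencies will be compared with the Fisher’s exact test"

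The test level is "0.05 (two-sided) for all tests". The section treats P-values as exploratory and concedes that adequate power is out of reach. Under Sample size, 25 patients per arm are fixed in advance without a calculation, and the section adds: "The results of this exploratory analysis could serve as the basis for a further prospective randomized study with a statistically justified sample size".

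**The concern.** The article gives the primary count the test that it otherwise uses for frequencies. To run it, someone must first turn the count into categories, and the article does not say how. A split at zero treats 1 new lesion and 20 new lesions alike. A table with one column per observed count keeps the values but ignores their order. In either case the size of a treatment effect on lesion number is largely lost, and the undeclared cut-point leaves a choice open in the primary analysis.

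This is more than detail left to a fuller document. The article names the test, and a statistical analysis plan that follows it would inherit the mismatch. At stake are the efficiency of the main comparison in a trial of only 50 patients, and the form of the primary result: Fisher's test gives no rate ratio, which a later trial with a count endpoint would need for planning.

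**Working it through.** **The text.** The endpoint is a count, the stated rule is that tests fit the scaling, Fisher's test is the plan's tool for frequencies, and the primary count is assigned Fisher's test. These statements do not fit together, and no outside figure is needed to see it.

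**Inputs from the article.** 25 per arm, 1:1 allocation, two-sided 0.05. The sample size comes from no formula and no power is stated, so there is no figure to reproduce.

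**Assumed inputs.** Counts are negative binomial with placebo mean m from 1 to 8, size s from 0.5 to 2 (dispersion 1/s from 2 to 0.5), and rate ratio RR of 0.5 or 0.3.

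**Method.** The probability of no new lesion is P(0) = (s/(s+m))^s on placebo and (s/(s+RR·m))^s on TSO. Power of Fisher's test on any versus none was obtained by summing over all 2×2 tables with 25 per arm. Mann-Whitney and a negative binomial likelihood-ratio test were simulated, 1,500 trials per scenario, so the simulation standard error is at most √(0.25/1500) = 1.3 percentage points.

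**One case by hand (m = 5, s = 1, RR = 0.5).** Placebo P(0) = 1/6 = 0.167; TSO P(0) = 1/3.5 = 0.286. A halved lesion rate becomes 83.3% versus 71.4% with any new lesion, a difference of 11.9 points. For scale, if one arm has 20 of 25 with a new lesion, the other must have 12 or fewer for Fisher's test to reach 0.05, a gap of 32 points. Fisher power is 10%; Mann-Whitney power is about 41 to 46% across separate simulation runs.

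**Power in % at s = 1.**

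| Placebo mean | RR | Fisher any/none | Mann-Whitney | Negative binomial | Mann-Whitney ÷ Fisher |
|---|---|---|---|---|---|
| 1 | 0.5 | 16.7 | 27.7 | 35.0 | 1.7 |
| 1 | 0.3 | 41.4 | 63.3 | 73.5 | 1.5 |
| 2 | 0.5 | 16.7 | 35.4 | 45.8 | 2.1 |
| 2 | 0.3 | 48.1 | 71.9 | 83.9 | 1.5 |
| 4 | 0.5 | 10.8 | 42.5 | 55.1 | 3.9 |
| 4 | 0.3 | 37.4 | 83.4 | 92.6 | 2.2 |
| 8 | 0.5 | 7.0 | 47.7 | 60.3 | 6.8 |
| 8 | 0.3 | 24.8 | 89.5 | 96.7 | 3.6 |

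**Rest of the range.** At means of 1 to 2 the Mann-Whitney to Fisher ratio runs from about 1.3 to 2.4. At means of 3 or more it starts at about 1.7. The extreme is m = 8, s = 2, RR = 0.5: 96.0% and 88.9% have a new lesion, so Fisher power is 2.5% against 74.9%, about 30-fold. Fisher's test was the weaker in every scenario with an effect.

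**Other readings of the named test (m = 4, s = 1, RR = 0.5, separate simulation).** Any versus none 11%, split at the pooled median 27%, unordered exact test on the ungrouped counts 15%, Mann-Whitney 45%. A median split loses less; the unordered test does not rescue the analysis.

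**Behaviour without an effect.** The null rejection rate was about 0 to 3% for Fisher, 4 to 5.5% for Mann-Whitney and 5 to 7% for the negative binomial test. The negative binomial power is therefore slightly overstated.

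**The case against.** The best defence is that this is a declared pilot. Its P-values are exploratory, it concedes low power, and no confirmatory decision rests on this test. Even the better tests stay modest: in the case worked by hand, Mann-Whitney reaches less than 50%. This stands and lowers the severity. It does not explain why the less efficient test was chosen for the few patients available.

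Four stronger readings are tempting, and the documents do not support them.

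- **The choice always cuts power several-fold, or leaves the primary result nearly uninformative.** That needs a lesion rate, and none is given. Eligibility admits CIS patients and patients whose only MRI activity is one enlarging T2 lesion, so a mean of 1 to 2 cannot be excluded. There the ratio is at most about 2.4.
- **The pilot cannot inform the next trial.** Means, variances and rates can be computed from the recorded counts whichever test supplies the P-value. The article says only that the results could serve as a basis, and it does not rule out estimates in the full plan.
- **Earlier dropout on TSO would mimic benefit.** Suppose 20% of TSO patients and no placebo patients stop at month 6, with no true effect, m = 5 and s = 1. The lesion-free proportion on TSO moves from 16.7% to 0.8 × 16.7% + 0.2 × 28.6% = 19.0%, and Fisher's rejection rate only from 2.1% to 2.5%. Handling of early withdrawal may also sit in the full plan.
- **The primary analysis merely repeats a secondary endpoint.** The lesion-free endpoint also involves T1 hypointense lesions. A split at zero T2 lesions would largely overlap with it but is not identical.

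**Conclusion.** The concern holds as a mismatch between endpoint and test. A per-patient count is assigned a test for categories, no categories are defined, and the article's own rule on scaling is not followed. That part rests on the text alone.

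The size of the loss rests on assumed negative binomial counts with size 0.5 to 2, rate ratio 0.3 to 0.5 and 25 per arm, and on reading Fisher's test as any versus none. Under those assumptions Mann-Whitney has about 1.3 to 2.4 times the power at placebo means of 1 to 2, and about 1.7-fold to several-fold at means of 3 to 8. Since P-values are exploratory, this is a should-fix.

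**What to change.** In Statistical methods, replace the sentence on the primary endpoint. At minimum, use the Mann-Whitney test already in the plan, or a Wilcoxon test stratified by sex and disease course, which are the randomization strata. Accompany it with a negative binomial rate ratio, its 95% CI and the dispersion estimate, so that the primary result can inform the next trial. If the negative binomial test is made primary instead, report a permutation or rank P-value beside it, because its simulated type I error was 5 to 7% at this sample size. Keep Fisher's exact test for proportions, including the lesion-free endpoint.

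The cost is a wording change in the protocol and analysis plan, made before unblinding; no new data are needed. The small downside is a distributional assumption for the rate ratio, which the rank or permutation analysis covers.

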### Randomization and interventions

The eligibility of patients will be determined at the screening visit. At the baseline visit, patients who qualified for participation in the study will be stratified according to gender and disease course (RRMS/CIS) and randomized 1:1 into the two intervention groups. One group will receive TSO 2,500 eggs orally every 14 days, the other a placebo suspension orally every 14 days. Visits will be carried out after 3, 6, 9 and 12 months (Table 2). To ensure reliable monitoring of tolerability, telephone check-ups are planned after every dispensation if a patient does not visit the study center, because prior studies have shown frequent gastrointestinal adverse events or symptoms after therapy with TSO [18]. Optional follow-up visits will be offered at 15 and 18 months after randomization. If necessary, additional unscheduled visits can be performed at any time.

**Table 2 T2:** Time schedule of regular study visits

	**Screening**	**Random (month 0)**	**Tel.V1 -6 (week 0, 2, 4, 6, 8, 10, 16, 20, 28, 32, 40, 44) ± 3 days**	**V1 (month 3) ± 10 days**	**V2 (month 6) ± 10 days**	**V3 (month 9) ± 10 days**	**V4 (month 12) ± 10 days**	**V5 (month 15) ± 10 days **** *(optional)* **	**V6 (month 18) ± 10 days **** *(optional)* **
Informed consent	x								
In/exclusion criteria	x	x							
Randomization		x							
Demographic data	x								
Pregnancy test	x								
Confirmation of MS diagnosis	x								
Relapse history	x	x		x	x	x	x	x	x
Medical history	x	x		x	x	x	x	x	x
Physical examination	x			x	x	x	x		x
Vital signs	x	x		x	x	x	x		x
Weight	x						x		x
MSFC	x						x		x
EDSS	x		x	x	x	x	x		x
Safety lab	x			x	x	x	x		x
Immunological sampling		x		x	x	x	x		x
MRI	x				x	x	x	optional	optional
AE/SAE				x	x	x	x	x	x
Questionnaires (fatigue, depression)	x	x			x	x	x	x	x
Drug supply		x	x	x	x	x			
Drug account					x		x		

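### The named Mann–Whitney tests use neither the pre-treatment values nor the randomisation strata, an avoidable loss of efficiency for the secondary endpoints measured at baseline

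*Protocol article*

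**What the plan says.** All references are to the protocol article.

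- **Randomization and interventions:** patients are "stratified according to gender and disease course (RRMS/CIS) and randomized 1:1 into the two intervention groups".
- **Table 2:** MRI, EDSS and MSFC are marked at screening, and the fatigue and depression questionnaires at screening and month 0. Pre-treatment T2 lesion volume, brain volume, EDSS, MSFC, BDI and FSS will therefore be available.
- **Outcome parameters:** these measures are all listed as secondary endpoints.
- **Statistical methods:** "Secondary endpoints will be analyzed non-parametrically using Mann–Whitney-U-test, due to the small sample size and possible deviations from normality". Fisher's exact test is named for the primary endpoint and for frequencies. No stratified test, covariate or baseline adjustment is named.
- **Sample size:** a "sample size of 25 patients per intervention arm, giving a total of 50 patients", chosen because existing data "are insufficient for an exact statistical sample size calculation".
- **Power and test level:** Statistical methods concedes "Due to the restricted sample size of the pilot study, sufficiently powerful statistical analysis is not possible". The test level "is defined as *P* = 0.05 (two-sided) for all tests".

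**The concern.** The design balances two factors and collects a pre-treatment value for most continuous and ordinal secondary endpoints, but the named test leaves both out. Where an endpoint is correlated with its own baseline, part of the between-patient spread is predictable and can be removed without recruiting anyone. A trial that admits to low power has good reason to do so.

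The stated reason for Mann–Whitney is small numbers and possible non-normality. That justifies a rank-based method. It does not justify an unadjusted one, because rank-ANCOVA meets the same reason.

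At stake is the precision of the secondary contrasts. The Sample size section says the results could be the basis for a further, properly sized trial.

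**Working it through.** **Inputs from the article.** 25 per arm, two-sided 0.05. The total reproduces (2 × 25 = 50). There is no stated effect size, SD or power to reproduce.

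**Assumed inputs (not in the article).** Effect 0.4 SD on the log scale; correlation r between baseline and final value of 0.3, 0.5, 0.7 and 0.9; equal variances; no dropout.

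**Step 1: variance of the treatment contrast, relative to final values.**

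- Final value: 1
- Change from baseline: 2(1 − r)
- Baseline-adjusted: 1 − r²

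| r | Change, 2(1 − r) | Adjusted, 1 − r² | Adjusted ÷ change = (1 + r)/2 |
|---|---|---|---|
| 0.3 | 1.40 | 0.91 | 0.65 |
| 0.5 | 1.00 | 0.75 | 0.75 |
| 0.7 | 0.60 | 0.51 | 0.85 |
| 0.9 | 0.20 | 0.19 | 0.95 |

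Adjustment is never worse than either unadjusted choice in this formula. Its advantage over final values grows with r, and its advantage over change scores shrinks with r. The equivalent total sample size against final values is 50/(1 − r²), about 55, 67 and 98 at r = 0.3, 0.5 and 0.7.

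**Step 2: simulated power, 25 per arm, effect 0.4 SD on the log scale.**

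| r | Mann–Whitney, final value | Mann–Whitney, log change | Rank-ANCOVA |
|---|---|---|---|
| 0.3 | about 26% | 20% | 28% |
| 0.5 | about 26% | 27% | 33% |
| 0.7 | about 26% | 40% | 44% |
| 0.9 | about 26% | 86% | 83% |

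- Rank-ANCOVA minus final value: about 2, 7, 18 and 57 points.
- Rank-ANCOVA minus log change: 8, 6, 4 and −3 points.
- The type I error of rank-ANCOVA stays near 0.05.
- At r = 0.9 rank-ANCOVA falls slightly behind log change, because ranking loses a little information and Step 1 leaves only a 5% variance advantage.

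**Step 3: a second effect size.** At 0.5 SD, Mann–Whitney on final values has power 0.38 to 0.39. Rank-ANCOVA has 0.42, 0.47 and 0.62 at r = 0.3, 0.5 and 0.7, and Mann–Whitney on change has 0.29, 0.38 and 0.57. The pattern is the same.

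**Step 4: strata alone.** Let R² be the assumed share of outcome variance that gender and disease course explain. The equivalent sample size is 50/(1 − R²): 51.0 at R² = 0.02 and 62.5 at R² = 0.20. Simulated power at 0.5 SD moves from 0.38 to 0.40 at R² = 0.02 and from 0.36 to 0.46 at R² = 0.20. If the strata are ignored in the analysis, the Mann–Whitney type I error is 0.045 and 0.026 respectively. That is conservative, not inflated.

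**The case against.** **The article does not say that Mann–Whitney is applied to final values.** Some endpoints are changes by description, such as brain atrophy, brain metabolism and EDSS progression. This stands. A reader might infer from the 26% against 83% at r = 0.9 that the plan forfeits most of its power, but that holds only for final values. On log change the advantage is 4 to 8 points up to r = 0.7 and gone at 0.9.

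**The trial is an exploratory pilot that concedes low power, and unadjusted tests are valid.** This also stands. A reader might infer that uncorrected chance imbalance biases the comparison. It does not: the type I error already allows for it, and stratified randomisation balances gender and disease course by design.

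**A condensed article leaves covariates to the full protocol or analysis plan.** This stands only in part. The article names the tests and gives a reason for them, so the point is to replace a stated method, not to fill in a missing detail.

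**The argument might be extended to relapses and the primary endpoint.** The documents do not support this.

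- *Relapse rate.* Annualising can distort ranks: one relapse with exit at month 3 becomes 4 per year and outranks two relapses in 12 months. With assumed rates of 0.8 and 0.4 and 20% dropout, however, simulated power was 27% for Mann–Whitney and 29% for a negative binomial model with a follow-up-time offset. A Poisson model reached 39%, but with 8.5% type I error.
- *Primary endpoint.* As written it is tested by Fisher's exact test, so there is no count model to which screening Gd+ activity could be added. In simulated count models the variance ratio from adding it was 0.97 to 1.71, which includes no gain.

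**Conclusion.** The point holds as an efficiency weakness, confined to continuous and ordinal secondary endpoints that have a same-variable baseline. It is not a validity error.

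Its size depends on what Mann–Whitney is applied to. Against final values the gain runs from about 2 points of power at r = 0.3 to 57 at r = 0.9. Against log change it is modest up to r = 0.7 and nil at 0.9. The gain from the strata alone is probably small. The effect size, correlations and R² behind these figures are all assumptions, since the article gives none.

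The change is still worth making. The correlations will differ between endpoints and are not known in advance. Adjustment does about as well as the better unadjusted choice, or better, across the whole assumed range, whereas final values do badly at high r and change scores at low r.

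**What to change.** In Statistical methods, state that continuous and ordinal secondary endpoints with a pre-treatment value of the same variable (T2 lesion volume, brain volume, EDSS, MSFC, BDI, FSS) will be analysed by rank-ANCOVA, or by ANCOVA with a permutation p-value. The covariates are the baseline value, gender and disease course. Keep the unadjusted Mann–Whitney test as a sensitivity analysis, and say whether it uses final values or change.

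A model with a follow-up-time offset for relapses is optional. If used, it must allow for overdispersion. No covariate change to the primary endpoint is asked for here.

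The cost is a few lines of code and a few degrees of freedom. All covariates are already scheduled, and no patient, visit or assessment is added.

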### Blinding

Both the patients and all study personnel will remain blinded throughout the complete treatment period of 12 months. Treatment allocations will only be disclosed after the final database lock or in case of emergency. The active study therapy and placebo bottles will be supplied by OVAMED GmbH and labeling of bottles and randomization of patients will be performed in the central pharmacy of the Charité - Universitätsmedizin Berlin. The patients will mainly be attended to by a “treating physician”, responsible for evaluating the inclusion or exclusion criteria, adverse events, relapses, side effects and so on. All neurological examinations will be performed by an independent “evaluating physician”. To separate the physicians’ function in a threating and an evaluating position in order to prevent unblinding is necessary because patients under therapy with TSO commonly report gastrointestinal side effects that may point the physician to the verum therapy. Similarly, evaluation of all other paraclinical parameters, including MRI, will be conducted by independent examiners. Any patient-related crosstalk between treating and evaluating physicians or examiners will be prohibited unless required for safety reasons. A simple unblinding procedure has been designed, which allows for rapid unblinding of a patient in case of a medical necessity. If the patient is unblinded, he or she will be automatically excluded from the study.

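### Fisher's exact test on the relapse-free proportion cannot use time under observation, so unequal early exit can bias it; for the annualized relapse rate, Mann-Whitney costs only some efficiency

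*Protocol article*

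**What the plan says.** Under Outcome parameters the protocol article names two relapse endpoints: "Other secondary clinical endpoints include the annualized relapse rate and the proportion of relapse-free patients". Under Statistical methods it assigns tests by type of variable: "Secondary endpoints will be analyzed non-parametrically using Mann–Whitney-U-test", and "Frequencies will be compared with the Fisher’s exact test". The relapse-free proportion is a frequency and falls to Fisher's test. The annualized relapse rate is a numerical secondary endpoint and falls to Mann-Whitney. The level is "0.05 (two-sided) for all tests", without adjustment, and all P-values are declared exploratory.

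A general clause in the same section promises tests suited to scale and distribution, but it does not mention length of observation. No time-to-first-relapse analysis, person-time weighting or offset is named. Both intention-to-treat and per-protocol analyses are planned.

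On follow-up, Randomization and interventions says "Visits will be carried out after 3, 6, 9 and 12 months". Blinding says that unblinded patients leave the study and that "patients under therapy with TSO commonly report gastrointestinal side effects". The article gives no expected dropout and no rule for classifying patients who leave before month 12.

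**The concern.** A 2x2 table has no cell for a patient who was relapse-free until leaving at month 2. Whoever fills in the table must call that patient relapse-free, call the patient a failure, impute, or drop the patient. Each choice moves the estimate when exit differs between arms.

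The annualized rate is different because time is its denominator. Yet in a rank test of individual rates, a zero from two months ties with a zero from twelve. One relapse before leaving at month 2 becomes 1/(2/12) = 6 per year and goes to the top of the ranking.

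These are the clinical relapse endpoints of a pilot whose results, according to Sample size, could form the basis of a larger trial. A relapse-free difference shifted by several points, or a P-value with no matching rate ratio, is a poor input to that planning.

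**Working it through.** **Inputs from the protocol article.** "determined sample size of 25 patients per intervention arm, giving a total of 50 patients" (Sample size); "randomized 1:1 into the two intervention groups" (Randomization and interventions); 12 months of treatment; two-sided 0.05. The sample size was set without a calculation, so there is no stated power to reproduce.

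**Assumptions, not in the article.** Relapses follow a Poisson process with rate L per year. Leavers exit uniformly between 0.03 and 0.5 year, and exit is unrelated to relapse.

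**1. Relapse-free proportion, no true effect, leavers without relapse counted as relapse-free.**
- Completers: exp(-L). At L = 0.6 this is 0.549.
- Leavers: [exp(-0.03L) - exp(-0.5L)] / (0.47L) = (0.982 - 0.741)/0.282 = 0.856.
- Arm with exit share d: (1 - d) x 0.549 + d x 0.856. This gives 0.564 at 5%, 0.610 at 20% and 0.641 at 30%.
- False difference at 20% v 5%: 0.610 - 0.564 = 4.6 points, or 0.046 x 25 = 1.2 patients.
- False difference at 30% v 5%: 0.641 - 0.564 = 7.7 points, or 0.077 x 25 = 1.9 patients.
- For L from 0.4 to 1.0, the 30% v 5% figure runs from 5.8 to 10.2 points.
- With exit spread over 12 months and L = 0.7, completers are 49.7% and leavers 71.9% relapse-free. Exit of 10% v 30% then gives 0.20 x 22.2 = 4.4 points.

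**2. The direction depends on the rule** (L = 0.6, 30% v 5% exit).
- Leavers counted as failures: 0.70 x 0.549 = 0.384 against 0.95 x 0.549 = 0.521, so the arm with more exit looks 13.7 points worse.
- Only relapse-free leavers dropped: 0.384/(0.70 + 0.30 x 0.144) = 0.517 against 0.521/(0.95 + 0.05 x 0.144) = 0.545, about 3 points worse.
- All leavers dropped: 0.549 in both arms, no bias under these assumptions.

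**3. Equal exit.** There is no false difference. With 0.7 v 0.25 per year and 20% leaving each arm (exit over 12 months), a true difference of about 28 points shrinks to about 26, and Fisher's power falls from 45% to 38%.

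**4. Annualized rate, bias.** For a patient watched for time f, the expected count is L x f, so the expected count/f is L whatever f is. In simulation with L = 0.7 in both arms, mean rates stayed at about 0.70 in each arm at every exit pattern. The probability that a TSO patient ranks lower than a placebo patient drifted from 0.50 only to 0.514 (placebo 10%, TSO 30% exit) and 0.526 (10%, 50%).

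**5. Power by simulation** (0.3 v 0.9 per year, 25 per arm, 20% exit in each arm within six months).

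| Comparison | Planned test | Alternative | Range over repeat runs |
|---|---|---|---|
| Relapse-free | Fisher 48% | log-rank 63% | 48-54% v 61-64% |
| Rate, Poisson | Mann-Whitney 64% | rate model 68% | 62-65% v 68% |
| Rate, frailty variance 0.5 | Mann-Whitney 52% | rate model 58% | 51-53% v 58-61% |

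With no exit at all, Fisher has 62% and log-rank 70%. So 8 of the 63 - 48 = 15 points have nothing to do with exit. They reflect Fisher's conservatism and the yes/no coding. Boschloo's test on the same table reaches 59% with 20% exit.

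**6. False-positive rate** (0.6 per year in both arms).
- 30% v 5% exit within six months: Fisher 5.2%, Mann-Whitney 6.8-7.6%, rate model 4.0-4.6%.
- 20% v 5%: Fisher 3.4-3.6%, Mann-Whitney 5.2-5.4%.
- 30% v 5% spread over 12 months: Fisher 4.2%, Mann-Whitney 5.4%.

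**The case against.** The bias in the relapse-free comparison needs two things the article does not state: unequal exit, and a rule that counts leavers as relapse-free. Such a rule may stand in the full protocol or analysis plan, and its absence here is no fault. The intention-to-treat commitment fits continued observation after stopping treatment, in which case little follow-up time is lost. Gastrointestinal effects are mentioned as a threat to blinding, not as a reason for leaving, and the Abstract expects good tolerability. All of this stands, and it makes the bias conditional. It does not remove the point that the named test cannot use observation time under any rule.

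A reader might infer that both relapse comparisons ignore follow-up. That is not so: annualizing divides by time, and the mean rate is unbiased. A reader might also infer that the tests generate false positives. Outside the extreme early-exit scenario, rejection stays near 5%.

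About half of Fisher's power gap against log-rank would exist with complete follow-up. The article gives a reason for rank tests, namely small numbers and possible non-normality, and it claims no power. The alternatives were also simulated with exit unrelated to relapse, which suits Kaplan-Meier. These points stand and lower the priority.

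**Conclusion.** The point holds in limited form. For the relapse-free proportion, the plan fixes a test that cannot use time under observation. If exit is unequal and leavers are counted as relapse-free, the arm losing more patients gains about 4 to 5 points (20% v 5%) or about 8 points (30% v 5%), that is, one to two patients of 25. This rests on 0.6 relapses per year and exit within six months. With equal exit there is attenuation and lost power, but no false effect.

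For the annualized rate there is no bias in the mean. The cost is a modest efficiency loss, roughly 4 to 8 power points at 20% exit (3 to 9 across repeat runs), and no rate ratio with an interval. The documents do not support the stronger reading that unequal exit is expected or that both comparisons are biased. Because both endpoints are secondary and exploratory, the priority is optional to moderate.

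**What to change.** Replace the tests for these two endpoints under Statistical methods:
- **Relapse-free status:** Kaplan-Meier estimate at month 12 by arm, compared by a log-rank test, with patients censored at last contact.
- **Annualized relapse rate:** a robust Poisson or negative binomial model with log follow-up time as offset, reported as a rate ratio with 95% CI. Mann-Whitney may stay as a sensitivity analysis.
- **Exit:** report numbers, timing and reasons by arm.

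The cost is a few sentences and standard procedures in the software already named. Relapse-onset and last-contact dates are needed; Table 2 lists relapse history at the visits, but the article does not say that dates are recorded.

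There are two downsides. The rate model relies on large-sample standard errors at 25 per arm. The simulated size of the robust version was 4.0-4.9%, but the negative binomial version was not simulated. Censoring also assumes that exit is unrelated to relapse, which is why reasons for exit should be shown.
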